## Abstract

**Background:**

Up to 40% of individuals who sprain their ankle develop chronic ankle instability (CAI). One treatment option for this debilitating condition is joint mobilisation. There is preliminary evidence that Mulligan’s Mobilisation With Movement (MWM) is effective for treating patients with CAI, but the mechanisms by which it works are unclear, with Mulligan suggesting a repositioning of the fibula. This randomised controlled trial aims to determine the effects of MWM on anatomical and clinical characteristics of CAI.

**Methods:**

Participants 18 years or over with CAI will be accepted into the study if they satisfy the inclusion and exclusion criteria endorsed by the International Ankle Consortium. They will be randomised into the experimental group (MWM) or the placebo group (detuned laser) and will receive the assigned intervention over 4 weeks. General joint hypermobility and the presence of mechanical instability of the ankle will be recorded during the first visit. Further, position of the fibula, self-reported function, ankle dorsiflexion range, pressure pain threshold, pain intensity, and static and dynamic balance will be assessed at baseline, and at the conclusion of course of intervention. Follow-up data will be collected at the twelfth week and at the twelfth month following intervention.

**Discussion:**

Effectiveness of MWM on clinically relevant outcomes, including long term benefits will be evaluated. The capacity of MWM to reverse any positional fault of the fibula and the association of any positional fault with other clinically important outcomes for CAI will be explored. Proposed biomechanical mechanisms of fibular positional fault and other neurophysiological mechanisms that may explain the treatment effects of MWM will be further explored. The long term effectiveness of MWM in CAI will also be assessed.

**Trial registration:**

Australian New Zealand Clinical Trials Registry; ACTRN12617001467325 (17/10/2017).

## Background

Up to 40% of patients with an initial ankle sprain develop chronic ankle instability (CAI), which is frequently associated with recurrent sprains and persistent pain [1, 2]. A recurrent subjective perception of the ankle joint ‘giving way’ is clinically indicative of CAI [3], which is defined as “repetitive bouts of lateral ankle instability resulting in numerous ankle sprains” [4]. Clinical management of CAI often involves balance and sport-related activity training [5]. In a recent meta-analysis, preliminary evidence was also found supporting joint mobilisation as a clinically effective intervention in improving dynamic balance and dorsiflexion range of motion in CAI [6].

Several ankle joint mobilisation procedures have been developed and described by renowned manual therapists such as Geoffrey Maitland, Freddy Kaltenborn and Brian Mulligan, and are commonly used in rehabilitation [7]. These procedures are applied to a joint, either in the form of non-thrust passive joint mobilisations, high velocity thrust manipulation, or Mobilisation With Movement (MWM). MWM is defined as the application of a sustained passive accessory movement to a joint while the patient actively performs a task/movement that was previously identified as being painful or limited [8]. After manual application of MWM, tape is applied to help maintain the glide and corrected fibular position [9]. Biomechanically and neurophysiologically mediated mechanisms have been proposed to explain how these joint mobilisation procedures may work [8, 10]. The proposed neurophysiological mechanisms are based on animal [11] and human experiments [12] related to pain science and motor systems [8]. These have shown that joint manual therapy techniques including MWM, activate a descending pain inhibitory pathway which is non-opioid mediated [8]. One proposed biomechanical mechanism relates to a reduction of an entrapped meniscoid or synovial fringe by a specifically directed MWM glide particularly in those instances where only one repetition is required to bring about a substantial and long lasting effect [8].

Of our recent systematic review and meta-analysis identified greater effects for MWM and Mulligan taping compared to Maitland joint mobilisation (with and without traction) and joint thrust manipulation [6, 13]. Dorsiflexion range of motion and self-reported instability were some of the outcomes for which there was evidence of improvement from MWM, although the long term benefits were unclear [14–16]. Most of the previous studies on chronic ankle sprains have applied MWM to the talocrural joint [14–18], and few studies have applied MWM taping [19–21]. However Mulligan proposes that an anterior fibular positional fault commonly results from ankle inversion sprains, and that a MWM using a posterior glide of the fibula to correct this should be trialled after 48 h following such an injury [22]. Patients with recurrent ankle sprains may also benefit from this MWM treatment combined with taping aimed at maintaining the posterior fibula glide, with reportedly less ‘giving way’ and greater confidence in using the ankle in patients with functional instability and pain [22]. Therefore this study is designed to evaluate the clinical benefits of the fibular posterior glide MWM with Mulligan taping, and whether it corrects any demonstrable positional fault which may exist. The prevalence of pain in people with CAI is high (60.1%) [23] and to our knowledge no studies have assessed the effect of MWM on pain. In addition, the present study will assess the effects of MWM on pressure pain threshold in CAI. The presence of localized peripheral sensitization has been previously identified in acute inversion ankle sprains [24] and in subacute ankle sprains [25]. Balance impairments in CAI are frequently reported in the literature and MWM has been found to be effective immediately after application, but there is presently insufficient research to determine the short term benefits of MWM for balance impairments [6]. The present study plans to address this deficiency in the literature as well.

A positional fault at the inferior tibio-fibular joint, is one arthrokinematic abnormality proposed to be related to persistent/recurrent symptoms and repetitive ankle sprains in CAI [4]. In the case of an ankle joint sprain, Mulligan suggests that the distal fibula is ‘mal-positioned’ anteriorly (anterior positional fault) following an inversion injury and that chronicity may result if this remains uncorrected [22, 26]. Preliminary evidence for such an anterior fibular positional fault was identified in Hubbard et al’s study of individuals with CAI [27]. However it is unclear whether ankle instability caused the anterior fibular position or whether the fault itself was actually the predisposing factor to re-injury. Also, the clinical importance of an anterior fibular positional fault in relation to other potential contributors to CAI remains unclear. Further, the mechanism(s) of changes in CAI outcomes after MWM needs to be further investigated [15, 28]. It has been proposed by Mulligan in his positional fault hypothesis, that MWM effects an immediate and lasting improvement by correcting a minor bony incongruity which is the source of the patient’s presenting problem [22]. However, the capacity of MWM to reverse any positional fault remains unclear and further studies are required to assess the effectiveness of this technique.

The objective of this study is to determine the effect of MWM on anatomical and clinical characteristics of CAI, and to determine the long term effectiveness of this treatment.

The specific aims of the study are therefore:To evaluate the effectiveness of MWM on clinically relevant outcomes, including patient-reported outcomes (dorsiflexion range, pain intensity, self- reported function, pressure pain threshold, static and dynamic balance), including long lasting benefits assessed at 12 months post treatment.To assess the effect of MWM on changing the fibular position relative to the position of the tibia in CAI.

## Methods

### Design

This randomised controlled study has been registered in the Australian New Zealand Clinical Trial Registry (ANZTR) and ethical approval has been granted by the Human Research Ethics Committee of The University of Newcastle, Australia (H-2017-0354). Informed consent will be obtained in writing from all participants.

### Participants

Participants aged 18 years or over will be recruited from the general community in the Newcastle area of New South Wales, Australia through flyers posted on noticeboards in shopping centres, the University of Newcastle main campus, and various other public places. Recruitment advertising will also be via University of Newcastle social media channels. Volunteers with CAI will be accepted into the study if they satisfy the inclusion and exclusion criteria as endorsed by the International Ankle Consortium [29], except the time period for experiencing at least two episodes of giving way is changed from 6 months to 12 months to account for the seasonal nature of some sports (Table 1).

**Table 1 Tab1:** Inclusion and exclusion criteria

Inclusion criteria	Exclusion criteria
• A history of at least one significant ankle sprain; - Initial sprain must have occurred at least 12 months prior to study enrolment - Was associated with inflammatory symptoms - Created at least one interrupted day of desired physical activity - The most recent injury must have occurred more than 3 months prior to study enrolment	• A history of previous surgeries to the musculoskeletal structures (i.e., bones, joint structures, nerves) in either lower extremity • A history of a fracture in either lower extremity requiring realignment • Acute injury to musculoskeletal structures of other joints of the lower extremity in the previous 3 months that impacted joint integrity and function (i.e., sprains, fractures), resulting in at least one interrupted day of desired physical activity • Have conditions for which manual therapy is generally contraindicated (such as the presence of a tumour, fracture, rheumatoid arthritis, osteoporosis, prolonged history of steroid use, or severe vascular disease)
• A history of the previously injured ankle joint ‘giving way’ and/or recurrent sprain and/or ‘feelings of instability’ - Participants should report at least two episodes of giving way in the 12 months prior to study enrolment	• Have conditions for which radiological imaging is contraindicated (e.g., pregnancy)
• Self-reported ankle instability should be confirmed with the Cumberland Ankle Instability Tool (CAIT) (≤24)	• Have conditions for which taping is contraindicated (e.g., allergy to strapping tape)
• General self-reported foot and ankle function questionnaire minimum score (Foot and Ankle Ability Measure (FAAM): activities of daily living (ADL) subscale < 90%, sport subscale < 80%)	• Receiving concurrent treatment - The most recent treatment for the ankle condition should have been received at least a week prior to study enrolment
	• Inability to read English

Data collection will be carried out at the physiotherapy and radiography research laboratories of the School of Health Sciences, The University of Newcastle, Australia.

### Procedure

This trial will adopt a pragmatic randomized controlled trial design to allow for real world application of MWM in a randomized setting [30]. This design has been used by previously published trials of manual therapy to better reflect routine clinical practice [31–33]. It enhances the external validity, but still controls for threats to internal validity.

The initial screening will be performed over the telephone after the potential participant contacts the research team. The screening questions are to determine if the potential participant meets some of the inclusion/exclusion criteria (Table 1). If a potential participant appears eligible following the telephone interview, further screening will be carried out using two standardised questionnaires: the Foot and Ankle Ability Measure (FAAM) [34], which measures function, and the Cumberland Ankle Instability Tool (CAIT) [35], which measures ankle instability. A link to access these questionnaires on the Qualtrics online survey platform (Qualtrics, Provo, Utah, USA) will be sent to the potential participant, along with the participant information statement and the consent form, through an email. Once the potential participant returns their completed forms, their final eligibility will be determined according to their scores (FAAM: activities of daily living (ADL) subscale < 90%, sport subscale < 80%; CAIT ≤24) on the two screening questionnaires. The participant will then be contacted to schedule an appointment for data collection.

Consenting participants will be randomised into two groups: an experimental group who will receive MWM, and a control group who will receive a placebo (detuned laser). All of the participants will be assessed for general joint hypermobility using the Beighton score [36]. Mechanical ankle instability will be tested separately for each ankle using an X-ray while undergoing an anterior drawer stress test [37, 38]. The clinically important outcome measures will include; radiological imaging of fibular position with respect to the tibia (positional fault), dorsiflexion range of motion (DFROM), pressure pain threshold (PPT), pain intensity, function, static balance and dynamic balance. These procedures and outcome measures are further explained below. The researcher who collects the clinical measurements, and the radiographer taking the X-rays, will be blinded to the participant’s group (intervention) allocation. This researcher will remain blinded to the group allocation until the 3 month follow-up. The 12 month follow-up data will be collected using online questionnaires.

Each participant will be randomly allocated to a group to receive either MWM (active) treatment or detuned laser treatment (placebo) (these interventions are fully explained below). The participant will be blinded as to whether they are receiving an active or placebo intervention, however due to the nature of the interventions, the treating practitioner cannot be blinded. Participants will be randomly allocated to groups according to a computer generated (GraphPad Software, Inc., CA, USA) randomisation schedule by another researcher not involved in data collection using sealed opaque envelopes. Each envelope will contain a piece of paper printed with either ‘1’ or ‘0’, for which ‘1’ denotes ‘MWM’ group and ‘0’ denotes ‘placebo’ group. The treating practitioner will open the envelope and allocate the participant to a group according to the number in the envelope, and deliver the designated treatment accordingly.

Participants of both groups will attend for 2–8 treatment sessions over 4 weeks. The exact number of treatments needed to achieve an optimal change is not presently known, so a range allows the practitioner to exercise their clinical judgement. We have chosen two as the minimum number of treatments, because usual clinical practice would involve a minimum of two visits to enable re-assessment following the initial treatment [39]. The actual number of treatment sessions delivered to participants in each group will be determined according to the clinical judgement of the treating practitioner, who is a registered physiotherapist with a post-professional tertiary qualification in the field of manual therapy and more than 20 years of clinical experience in treating musculoskeletal conditions. The physiotherapist will also be individually instructed in the MWM intervention by an accredited member of the Mulligan Concept Teachers Association. The physiotherapist will conclude the course of intervention if the patient reports they have fully recovered or if no further improvement is possible up to a limit of eight sessions over a 4 week period. The number of sessions and the duration of each session will be recorded. The same measures taken at baseline will be repeated at the conclusion of the course of intervention, within a maximum of 4 days after the participant’s last intervention session. Further measurements will be repeated at the twelfth week with the exception of the imaging, and only self-report outcomes will be assessed at 12 months. Participants will be contacted by telephone every 4 weeks after finishing treatment for up to 1 year to record any new ankle injuries, any treatments undertaken, and their level of engagement in sport and other activities. Figure 1 describes the flow of the study.

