### Application of the intervention

Participants in the experimental group will be treated with a manual MWM technique to the ankle and will be taped after the intervention using the Mulligan approach [22] to attempt to maintain the effects of the MWM. The control group will receive a detuned (inactive) therapeutic laser treatment to the lateral region of the ankle. The number of treatment sessions delivered for each participant will be based on their symptomatic response to treatment, as determined by the clinical judgement of the treating practitioner. Each participant will be asked to avoid concurrent interventions during their participation in the study.

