### MWM intervention

The participant’s inferior tibio-fibular joint will be mobilised using Mulligan’s fibula MWM for dorsiflexion and/or inversion [22]. Initially, the technique will be performed in supine lying with the tibia resting on the treatment table and the foot unsupported off the table’s edge. The practitioner applies a sustained pain-free anteroposterior glide with a slight cephalad and lateral inclination to the distal fibula (lateral malleolus). This glide is maintained while the participant performs active inversion or dorsiflexion (depending on which is more limited in range) to end of range. There should be no pain with the active movement. At the end of range, the practitioner will apply and sustain overpressure to the active movement for a few seconds (or the participant will do so after appropriate instruction) [16, 22]. If dorsiflexion remains restricted, this technique can be progressed and performed in partial and/or full weight-bearing.

One treatment session will consist of three to five sets, with six to ten repetitions of the active movement in each set, with the actual dosage depending on the individual response of the participant [22]. Participants will receive between two to eight sessions according to the clinical reasoning of the practitioner, over a period of 4 weeks. After each session, Mulligan MWM taping will be applied in an attempt to replicate the sustained fibula glide [8]. Non-elastic tape will be applied to the ankle starting 2 cm anterior to the fibula and 1 cm proximal to the tip of the lateral malleolus. The tape will be spiralled obliquely around the lower limb while the fibula glide is sustained, finishing on the anterior aspect of the leg [22]. The participant will be instructed to keep the tape on for 24 h. In the case of an adverse reaction, they will be advised to remove the tape immediately and note the length of time the tape was in place.

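### The post-treatment visit has no minimum interval after the last session, so MWM participants alone can be imaged and tested within their 24 h tape-wear period

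*Protocol article*

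**What the plan says.** Four statements in the protocol article bear on this point.

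- **Timing (Procedure).** The measures from baseline "will be repeated at the conclusion of the course of intervention, within a maximum of 4 days after" the last session. No minimum interval is given. Imaging is not repeated at week 12, and the 12-month follow-up is by online questionnaire.
- **Tape (MWM intervention).** "After each session, Mulligan MWM taping will be applied in an attempt to replicate the sustained fibula glide". The wear time follows: "The participant will be instructed to keep the tape on for 24 h".
- **One arm only (Application of the intervention; Detuned laser intervention).** The experimental group "will be taped after the intervention using the Mulligan approach". The control group receives detuned laser with the probe held off the skin. No tape or sham tape is described for it.
- **Blinding (Procedure).** "The researcher who collects the clinical measurements, and the radiographer taking the X-rays, will be blinded" to group allocation. For the researcher taking the clinical measurements, this is to last until the 3-month follow-up.

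Nothing in the article says that the tape must be off, or the ankle covered, before the post-treatment assessment.

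**The concern.** Each statement is reasonable alone, but nothing links the visit window to the wear period. Two things are at stake.

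**What is measured.** The second specific aim is the effect of MWM on fibular position relative to the tibia. The Background gives the purpose of the tape as holding the glide and the corrected position, which is the quantity the X-ray measures. If some MWM participants are imaged with tape on or just removed, and others a day or more after it came off, the arm's mean combines two different quantities. No later image exists to separate them. Dorsiflexion and balance are exposed in the same way, since they too could be tested with the ankle taped.

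**Who knows the allocation.** Tape occurs in one arm only, so seeing it identifies the arm. Static balance is tested barefoot, the algometer is applied to the skin around the ankle, and leg position is watched during the X-ray. Tape would be hard to miss in these tests.

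**Working it through.** The plan has no calculated figure on this point to reproduce. The check compares two time intervals, and no sample size or power figure depends on it.

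**Inputs**

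- Latest permitted visit: 4 days after the last session (Procedure), which is 4 × 24 = 96 h.
- Earliest permitted visit: not stated, so 0 h.
- Instructed tape wear after the last session, MWM arm: 24 h (MWM intervention).
- Tape in the control arm: none described.
- Planned size: 16 per group, allowing for drop-out (Sample size and data analysis). It is used here only to turn a share into a count.

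**Step 1: set the intervals side by side**

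| Time since last session | Visit permitted? | MWM arm | Control arm |
|---|---|---|---|
| 0 to 24 h | Yes | Tape on as instructed, or taken off early | No tape |
| More than 24 h, up to 96 h | Yes | Wear period over | No tape |
| More than 96 h | No | – | – |

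The arms are comparable in this respect only in the second row.

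**Step 2: size of the overlap**

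Overlap ÷ window = 24 ÷ 96 = 25%. The window left after the wear period is 96 − 24 = 72 h.

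**Step 3: participants affected**

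The article does not say when visits will fall, so the share of MWM participants seen within 24 h can be anything from 0 to 100%, or 0 to 16 of the 16 planned. If visits spread evenly over the 96 h (an assumption), the expected number is 0.25 × 16 = 4. Drop-out before the visit would lower these counts.

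**Step 4: outcomes exposed**

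- *Fibular X-ray:* exposed to tape acting on the measured quantity, with no later image as a check.
- *Dorsiflexion, static and dynamic balance:* exposed to tape on the ankle and to an assessor who can see it.
- *Pressure pain threshold:* one site lies anterior to the lateral malleolus, and the tape starts 2 cm anterior to the fibula. Testing there on skin may require the tape to come off, which can itself reveal the arm if done at the visit.
- *FAAM (primary), pain VAS, FAOS and PSFS:* self-reported, so little affected by assessor unblinding.

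**The case against.** The strongest reply is that this is a possibility, not a stated event. No sentence says that anyone will be assessed within 24 h or with tape on. The article condenses a fuller protocol, where a booking rule or an instruction to remove tape may stand. The repeated measures are meant to match those at baseline, when no study tape was worn, and the skin-contact test makes taped measurement less likely. This limits what can be claimed. It does not close the gap, because the article itself fixes the window, the wear time, the one-arm taping and the blinding, and as fixed they allow the overlap.

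Several stronger readings are tempting but not supported:

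- *That the positional-fault aim is defeated.* The Background describes the treatment under study as MWM with Mulligan taping, and the Discussion asks whether a reversal is evident 4 weeks after treatment starts. Taped images would blur the interpretation for those participants; they would not void the aim.
- *That the bias favours MWM.* Tape in one arm makes the error differ between arms, but the documents do not give its sign. Non-elastic tape might help or hinder dorsiflexion or reach.
- *That an early visit must show the tape to the assessor.* It could be taken off elsewhere beforehand, and a next-day visit can fall after the 24 h.
- *That unblinding carries into week 12.* The same researcher is meant to stay blinded until then, but carry-over would require recall of individual allocations. Nothing in the documents supports or measures that.
- *That same-day visits will be common because they are convenient.* The documents say nothing on this. The last session depends on the practitioner's judgement and may not be known in advance.

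**Conclusion.** The point holds as a gap in the timing rule. The visit window lacks a lower limit relative to tape wear that occurs in one arm only. A fully compliant visit can therefore confound the sole post-baseline X-ray and the assessor-measured outcomes with tape, and can disclose the allocation.

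The overlap of 24 in 96 h is certain from the text. How many participants fall in it is not: the range is none to all, and about a quarter holds only under even spread. The direction of bias is not established. The effect is confined to the post-treatment visit and mainly to secondary and mechanistic outcomes. The self-reported FAAM is little affected by assessor unblinding, and the sample size does not change.

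The change is still worth making before recruitment. It costs almost nothing, and no later analysis can take tape out of an image or restore blinding once lost.

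**What to change.** Leave the tape-wear instruction as it is and reconcile the visit window and the blinding statement with it:

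1. In both arms, schedule the post-treatment assessment after the stated tape-wear period following the last session has ended, and within the existing 4-day maximum. Applying the same rule to controls keeps timing comparable between arms.
2. Require tape to be off before the participant meets the blinded assessor or the radiographer, confirmed for example at booking or by staff who already know the allocation.
3. Record hours from the last session to the assessment for every participant, so that compliance and balance between arms can be reported.

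If a fuller protocol already contains such a rule, stating it in the Procedure section is enough.

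The cost is a booking window narrowed from 96 h to about 72 h, plus one recorded time. No visit or procedure is added.
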